**5.3.2 Specific Objectives**

1. To assess the prevalence and associated factors of IPV during pregnancy
2. To explore the community's perspectives of IPV during pregnancy
3. To evaluate the effect of couple-based violence prevention education on couples knowledge, attitudes, and controlling behavior towards IPV during pregnancy
4. To compare the effect of couple-based violence prevention education on the experience of IPV during pregnancy
5. To compare the effect of couple-based violence prevention education on women’s autonomy and self-efficacy

1. **Methods and Materials**

**6.1 Study area**

We will conduct the study in Hadiya Zone. It is one of the administrative zones in the Southern Nations, Nationalities, and Peoples Region (SNNPR). Its capital, Hossana Town, is located 235 km south-west of the capital city, Addis Ababa. Hadiya Zone has 13 woredas (districts) with an area of 3542.66 square kilometers and a population density of 444 people per square kilometer. The zone has four town administrations and 329 kebeles (sub-districts). According to 2021 Hadiya zone statistics, it has a total population of 1,767, 390 of whom 873,091 (49.4%) are males and 894,299 (50.6%) are females. Hadiya zone is bounded by 4 regions, namely: Oromia, Silte, Gurage, and Kembata, and one special zone, Yem (ZHD, 2021).

About 90% of the population lives in the rural part of the zone, and the dominant ethnic group is Hadiya. The zone has one comprehensive specialized hospital, three primary hospitals, sixty-one health centers, and 311 health posts (ZHD, 2021). The study will be conducted in four woredas of the zone, randomly selected from 13 woredas. Four-woredas (destricts) have 126 kebeles (the lowest administrative unit).

**6.2 Study period**

The study will take 8 months of follow-up (6 months of intervention + endline survey after 2 months of intervention) and be carried out for months from August 1, 2022, to April 30, 2023. The outcome information will be collected at baseline (≤12 weeks' gestation) and end-line (after 8 months of follow-up).

**6.3 Source population**

All couples (male partners and pregnant women of reproductive age) in Hadiya Zone

**6.4 Study population**

All couples whose wife is pregnant (1^st^ trimester) and in the child-bearing age in selected intervention and control clusters (kebeles)

**6.5 Inclusion and inclusion Criteria**

**Inclusion**

- Coupes whose wives are pregnant (1st trimester)
- Couples at least having one live birth
- Couples whose wives are of childbearing age
- Couples who lived in the study area at least six months before the study
- Couples living in the study area until 2 months after giving birth
- Couples whose wives' interpregnancy interval is less than two years
- Couples willing to be visited at home

**Exclusion**

- Couples having severe medical illnesses
- Couples with hearing or communication problems
- Couples with a plan to move out of the intervention and control clusters in the next 8 months

**6.6 Study variables**

**6.6.1 Dependent variables**

**Primary outcome variable**

- Intimate Partner Violence (experience versus not experiencing IPV)

**Secondary outcome variables**

- Knowledge, attitudes, and control towards IPV during pregnancy
- Knowledge: Good versus Poor Knowledge,
- Attitude: supportive versus not supportive attitude toward IPV
- Controlling behavior: yes versus no
- Women’s autonomy and self-efficacy

**6.6.2 Independent or ecological model variables**

**Individual**: wife age, wife age at marriage, spousal age difference, educational status of couple, occupation of couples, woman’s parity, alcohol use, sex of previous children, birth order smoking, previous ANC and place of delivery.

**Relational:** marriage type, duration of marriage, disparity in education level

**Community**: presence of social support and inequitable gender norms

**Societal**: household wealth index

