**Negative health behavior**

Antenatal alcohol and drug abuse

Smoking during pregnancy

Delayed prenatal care

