Intimate partner educational status was seen as a predictor of intimate partner violence. A systematic review and meta-analysis on intimate partner violence and associated factors in Ethiopia has found that pregnant mothers whose intimate male partner is unable to read and write are about three times more likely to experience IPV as compared to their literate counterparts (Alebel et al., 2018). In contrast, in a study done in Oman, there was no significant association between IPVp and pregnant women’s partner's educational status (Al Shidhani et al., 2020).

A systematic review and meta-analysis of intimate partner violence and associated factors among pregnant women by Alebel et al. (2018) in Ethiopia found that motherseducational status, partners’ educational status, and intimate partners’ alcohol use were significantly associated with IPV among pregnant women. In this analysis, the likelihood of intimate partner violence experience was two times higher among mothers who were unable to read and write as compared to their literate counterparts (Alebel et al., 2018).

Unintended pregnancy was the predictor of IPV studies in Oman, Bale, Ofla District, Tiray, Harari Region, and northern Ethiopia (Adhena et al., 2020; Al Shidhani et al., 2020; Gebrewahd et al., 2020; Lencha et al., 2019; Musa et al., 2020). A prospective observational study of pregnant women in Oman revealed that unplanned pregnancy was seen as a risk factor for IPV. Similarly, pregnant women who had an unwanted pregnancy were about three times more likely to encounter IPV than those who wanted the pregnancy, according to a cross-sectional study done in the Bale Zone, Southwest Ethiopia (Lencha et al., 2019). A contrasting result was reported in the systematic review and meta-analysis done by Alebel et al. (2020), which means the likelihood of IPV occurrence was two times higher among mothers’ who were unable to read and write as compared to their literate counterparts. That means unplanned pregnancy was not significantly associated with intimate partner violence (Alebel et al., 2018).

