**Intimate partner violence during pregnancy and maternal outcomes**

Experiencing intimate partner violence during pregnancy has been associated with a multitude of fatal and non-fatal health consequences for the mother and her baby (Alhusen et al., 2015; WHO, 2011a). Findings from research have shown that experiencing intimate partner violence during pregnancy leads to delayed early initiation of antenatal care or missed antenatal care appointments compared to non-abused counterparts. Findings on the association between intimate partner violence and maternal health care utilization from 36 national household surveys suggested that women experiencing intimate partner violence decreased maternal health care utilization in developing and middle-income countries. This review revealed that women who experience IPV during pregnancy were less likely to utilize four or more ANC visits, the number of ANC visits, and delivery care compared to their non-experienced counterparts (Leight and Wilson, 2021). In a similar way, a study conducted in Addis Ababa, Ethiopia, has shown that women who experienced physical intimate partner violence from male partners in their relationship are less likely to attend WHO-recommended four-month antenatal care compared to those who did not experience intimate partner violence. Likewise, women who experienced emotional and sexual IPV were less likely to attend the recommended ANC, which was attended by skilled delivery attendants, compared to their non-experienced counterparts (Leight and Wilson, 2021).

Smoking, alcohol use, substance use like chat chewing and inadequate weight gains during pregnancy are well-known risk factors for adverse neonatal outcomes. Similarly, study done by Bailey and Daugherty (2007) in US, found that Physical IPV during pregnancy increased rates of pregnancy smoking, increased rates of alcohol, marijuana, and harder illicit drug use around the time of conception. Moreover, the experience of psychological IPV during pregnancy significantly increased rate of alcohol use and an increased rate of pre-pregnancy obesity (Bailey and Daugherty, 2007). Researches have demonstrated that IPV during pregnancy is significantly associated with maternal depression, anxiety and stress, miscarriages, still birth and abortions (Afiaz et al., 2020, Alhusen et al., 2015, Belay et al., 2019, Kiranmai Devineni et al., 2018)

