**Reproductive**

Pregnancy intension, parity, sex of preceding birth, previous ANC follow-up, previous facility delivers,

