| 233 | How many quintals of the following legume do the family produced in this year? | | | | | 1.Bean  --------  2.pea  -------- | | | | 3. Lentil  -------  4.Nut  ------- | | | | | | 5. Chick pea  --------  6.grass pea  -----------  7.others,pecify | | | | |  | |
| 234 | How many kilograms of vegetables do the family produced? | | | | | 1.Gomen  2.Carrot  3.Potato | | | | 4. Tomato  5. Cabbage  6. Onion  10. Garlic | | | | | | 7.Beat root  8. Pumpkin  9.Pepper  11.Other specify | | | | |  | |
| 235 | How many kilograms of fruits do the family produced? | | | | | 1.Mango 2.Banana  3.Avocado | | | | 4. Papaya  5. Guava  6.Lemon | | | | | | 7. Other specify- | | | | |  | |
|  | **PART THREE: History of recent pregnancy and delivery** | | | | | | | | | | | | | | | | | | | | | |
| 301 | How many live births have you had? | | Enter number……………………………….. | | | | | | | | | | | | | | | | |  | | |
| 302 | Did you attend ANC for your recent pregnancy from skilled health personnel (nurse, mid-wife, and doctor or health officer)? | | Yes………………………….……………..….1  No……………………………………………..2 | | | | | | | | | | | | | | | | | If ‘**no**’  Skip to  **306** | | |
| 303 | If yes, where did you attend? | | Hospital..............................................................1  Health center…..................................................2  Health post/ clinic..............................................3  Home..................................................................4 | | | | | | | | | | | | | | | | |  | | |
| 304 | How many months pregnant were you when you first received antenatal care for the recent pregnancy? | | Enter the number months/weeks……………… | | | | | | | | | | | | | | | | |  | | |
| 305 | Has your baby’s father attended any antinatal visits with you for the most recent pregnancy? | | Yes……………………………….……………1  No………………….………………………….2 | | | | | | | | | | | | | | | | |  | | |
| 306 | Where did you deliver your recent baby? | | Hospital...........................................................1  Health center……….………………………….2  Health post/clinic……..……………………….3  Home…………….…………………………….4 | | | | | | | | | | | | | | | | |  | | |
| 307 | If it is at hospital or health center or health post/clinic, was the husband/partner present during labor or delivery? | | Yes ….………………………………………...1  No …………………………….………………2 | | | | | | | | | | | | | | | | |  | | |
|  | **PART FOUR: HISTORY OF CURRENT PREGNANCY** | | | | | | | | | | | | | | | | | | |  | | |

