| 708 | When I am confronted with a problem, I can usually find several solutions. | | | | | | 1 | | | | 2 | | | | 3 | | | | 4 |  | | |
| 709 | If I am in trouble, I can usually think of a solution | | | | | | 1 | | | | 2 | | | | 3 | | | | 4 |  | | |
| 710 | I can usually handle whatever comes my way. | | | | | | 1 | | | | 2 | | | | 3 | | | | 4 |  | | |
|  | **PART SEVEN: experience of intimate partner violence in the recent pregnancy(last pregnancy)** | | | | | | | | | | | | | | | | | | | | |  |
| 801 | **Physical** | | | | | | | | | | | | | | | | | | |  | |  |
|  | During recent pregnancy, did your partner: | Slap you or throw something at you Yes No  that could hurt you? ………………………………1 2  Push you, shove you or pull your hair……………..1 2  Hit you with his fist or with something  else that could hurt you?..........................................1 2  Kick you, drag you about or beat you up?...............1 2  Attempt to choke you or burn you on purpose?.......1 2  Threaten to use or actually use a gun,  Knife or other weapon against you? …..…………1 2 | | | | | | | | | | | | | | | | | |  | |  |
| 802 | **Psychological** | Yes No  Say or do something to humiliate  you in front of another person?....................1 2  Threaten to hurt or harm you or  someone you care about? ………………...1 2  Insult you or make you feel bad about yourself?...1 2  Do things to scare or intimidate you  on purpose (e.g., by the way he looked at you,  by yelling and smashing things)?...................1 2 | | | | | | | | | | | | | | | | | |  | |  |
|  | During your most recent pregnancy, did your partner: |  |  |  |  |  |  |  |  |  |  |  |  |  |  |  |  |  |  |  |  |  |
| 803 | **Sexual** |  | | | | | | | | | | | | | | | | | |  | |  |
|  | During your recent pregnancy, did your partner | Yes No  Physically force you to have sexual  intercourse with him when you did not want to?.....1 2  Force you with threats or in any other way  to perform sexual acts you did not want?.............1 2  Physically force you to perform any  other sexual acts you did not want to? …………....1 2 | | | | | | | | | | | | | | | | | |  | |  |
| 804 | If a woman is yes for 801 or 802 or 803, what did you do? | Nothing……………………………………………………..…..1  Reported to him relations…………………………………….....2  Quit relationship……………………………………………...…3 | | | | | | | | | | | | | | | | | | If ‘nothing’ skip to  805 | |  |

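### Objective 1 lists previous antenatal care and place of delivery as independent variables for violence, but the women's form asks about both for the same last pregnancy, so their direction can be reversed

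*Protocol*

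**What the plan says.** Objective 1 (section 5.3.2) is to assess the prevalence of IPV in pregnancy and the factors associated with it. Section 6.6.2 lists "previous ANC and place of delivery" among the individual-level independent variables. Figure 2 places "previous ANC follow-up, previous facility delivers" on the explanatory side as well.

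The literature review, under maternal outcomes, gives the opposite direction: "women who experience IPV during pregnancy were less likely to utilize four or more ANC visits, the number of ANC visits, and delivery care". Figure 1 lists "Delayed prenatal care" among the outcomes of violence; it does not mention place of delivery.

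Annex II, Part Three, item 302 asks "Did you attend ANC for your recent pregnancy from skilled health personnel", and item 306 asks where the most recent baby was delivered. The current pregnancy has its own Part Four. Part Seven is headed "experience of intimate partner violence in the recent pregnancy(last pregnancy". The Amharic heading in Annex VI likewise points to the pregnancy before this one.

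Section 6.17 gives a different window. Its scoring rules for sexual and emotional violence code a woman as unexposed when nothing has happened in the present pregnancy, and section 6.2 places baseline at 12 weeks or earlier.

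Section 6.24 names GEE for the intervention effect and states no model or covariate set for Objective 1.

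**The concern.** A variable offered as a factor associated with an outcome should not be something the outcome produces. The protocol argues that violence lowers use of care. It does not argue that ANC or place of delivery affects violence; neither appears among the predictors of violence reviewed under the factors associated with IPV. If care and violence are recorded for the same completed pregnancy, low ANC or home delivery may be reported as a risk factor when, on the protocol's own account, it is a consequence.

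A second effect arises if these variables share a multivariable model with education, wealth or parity. Adjusting for a consequence of the outcome biases the coefficient of any factor that also influences care use, and those are among the factors Objective 1 is meant to identify.

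A related inconsistency concerns pregnancy intention. Figure 2 includes it ("Pregnancy intension, parity, sex of preceding birth, previous ANC follow-up, previous facility delivers"), item 401 collects it, and the review supports it ("Unintended pregnancy was the predictor of IPV studies in Oman"), but section 6.6.2 omits it.

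**Working it through.** The plan states no figure on this point, so the first step is to order events in time under each window.

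**Step 1. Time order**

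| Window for violence | Source | ANC, previous pregnancy | Delivery, previous pregnancy |
|---|---|---|---|
| Last pregnancy | Annex II, Part Seven | Alongside the outcome | After the outcome |
| Current pregnancy | Section 6.17, sexual and emotional scoring | Before the outcome | Before the outcome |

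The word *previous* in section 6.6.2 settles the order only under the second window. Under the first, the care items and the violence items describe the same pregnancy.

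**Step 2. The reversed association itself**

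An odds ratio (OR) is symmetric. If violence lowers facility delivery with OR 0.8, 0.67, 0.5 or 0.33 within levels of other factors, and delivery has no effect on violence, a model for violence returns place of delivery as a protective factor with that same OR. These ORs are assumptions; the protocol gives none.

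**Step 3. Effect on another factor in a joint model**

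Inputs: IPV prevalence 37.5% (section 6.8). Assumed: an upstream factor X present in 50% of women, for example low education, with OR 2.0 for violence V; facility delivery D in 50%; OR of X for D 0.5; OR of V for D 0.5; no interaction and no effect of D on V.

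Because D depends on X and V without interaction, the OR of X for V given D is exactly

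OR(X,V) × [P(D|X=1,V=1) × P(D|X=0,V=0)] / [P(D|X=1,V=0) × P(D|X=0,V=1)].

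- P(V) is 0.295 when X=0 and 0.455 when X=1; the average is 0.375.
- P(D) for (X,V) = (0,0), (0,1), (1,0), (1,1) is 0.647, 0.478, 0.478, 0.314; the weighted average is 0.50.
- Adjusted OR = 2.0 × (0.3139 × 0.6466) / (0.4778 × 0.4778) = 2.0 × 0.2030 / 0.2283 = 1.78.

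The same calculation over the assumed range, true OR of X for violence 2.0:

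| OR of V for D | OR of X for D = 0.5 | OR of X for D = 0.33 |
|---|---|---|
| 1.0 | 2.00 | 2.00 |
| 0.8 | 1.92 | 1.88 |
| 0.67 | 1.87 | 1.80 |
| 0.5 | 1.78 | 1.66 |
| 0.33 | 1.66 | 1.49 |

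**Step 4. Both care variables, trial-sized samples**

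Simulation of 800 samples of 432 women. Assumed: IPV 37.5%, ANC 60%, facility delivery 50%, schooling 40%; schooling raises ANC and facility delivery with OR 2 to 3; violence lowers each with OR 0.5 to 0.7. Clustering was omitted.

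- True schooling OR 0.50: estimated at 0.56 to 0.72 with both care variables in the model; detected in 32 to 75% of samples, against 91 to 92% without them.
- No true schooling effect: estimated at 1.13 to 1.43; falsely significant in 8 to 36%, against 5 to 7%.
- Only place of delivery in the model: a true 0.50 becomes 0.52 to 0.59; false associations 5 to 10%.
- Both variables, but violence lowering care with OR only 0.8 to 0.9 and schooling OR 2: 0.52 to 0.53; false associations 5 to 6%.

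Steps 2 to 4 apply to the last-pregnancy window only.

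**The case against.** The strongest reply is that the listed variables are *previous* care. The review describes violence in a pregnancy reducing care in pregnancy; it does not say that violence now reduces care in an earlier pregnancy. Section 6.17 scores sexual and emotional violence in the current pregnancy, and section 6.24 speaks of violence during the trial period. On that reading previous care comes first and cannot be a consequence of the outcome. This stands. What remains is that earlier care may mark earlier violence by the same partner: section 6.5 requires a previous live birth and an interpregnancy interval under two years. A marker of that kind is not a consequence of the outcome, and the calculations above do not describe it.

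It is also fair that Objective 1 claims association only, that no joint model is stated for it, and that the covariate set may lie in an analysis plan not shown. A reader might infer that other factors will be distorted, or that the upper simulation values are expected. The document supports neither: the distortion is conditional on joint adjustment, and 0.72 and 36% are the extreme end of assumed inputs.

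A reader might also infer that Figure 1 names both variables as consequences, or that the trial result is biased. Figure 1 supports only the ANC half. Previous care belongs to a pregnancy completed before enrolment, so the education cannot alter it.

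On pregnancy intention, the same review section also reports a meta-analysis with no significant association. The omission is a minor list inconsistency that would not merit a point alone.

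None of this removes the conflict in the form as written, where violence and care refer to the same last pregnancy.

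**Conclusion.** The point holds in conditional form. With Annex II as written, place of delivery follows the recorded violence and ANC runs alongside it, so naming them as factors associated with IPV can reverse the direction given in the protocol's own review. That conclusion needs no joint model.

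Bias in other factors needs a joint model. Its size is unknown; under assumed odds ratios it runs from negligible (a true 0.50 read as 0.52) to moderate (0.72 at the extreme). Under the current-pregnancy window the reversal disappears and previous care is at most a marker of prior violence.

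The underlying fault is that section 6.17 and Annex II, Part Seven, name different pregnancies. The consequence considered here is confined to Objective 1; the randomised comparison is not affected by these variables.

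**What to change.** 1. Reconcile the outcome window between section 6.17 and Annex II, Part Seven (and Annex VI), and state one.
2. Where IPV is measured for the last pregnancy, remove ANC and place of delivery of that pregnancy from the explanatory variables for Objective 1 in section 6.6.2 and Figure 2. Report them descriptively or as possible consequences of violence.
3. Where IPV is measured for the current pregnancy, they may stay, with a sentence saying they may be markers of earlier violence.
4. Add pregnancy intention (item 401) to the individual-level list in section 6.6.2, to agree with Figure 2.

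The cost is a text edit to the variable list and to the wording of the window; the care items and pregnancy intention are already collected. The downside is that, under the last-pregnancy window, ANC and place of delivery are no longer reported as adjusted factors.

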Findings from the WHO multi-country study on women’s health and domestic violence have resulted in the finding that secondary and above education, high socioeconomic status of women, and formal marriage were protective factors of recent intimate partner violence. Whereas, young age, cohabitation, alcohol use, attitudes supportive of wife beating, having outside sexual partners, and experiencing childhood abuse were the risk factors of intimate partner violence (Abramsky et al., 2011). History of adverse pregnancy outcomes, partner age 30 and above, partner aggressive behavior, partner who chews chat and partner smoking status were significantly associated with intimate partner violence during pregnancy in a study done by Lencha B. et al. (2019) in Bale Zone, Southwest Ethiopia. Pregnant women whose partner was aged 30 years and older were about two times more likely to experience intimate partner violence during pregnancy (Lencha et al., 2019).

Studies have found that being single, fear of pregnancy complications, history of chronic illness, unintended pregnancy, history of stillbirth, intimate partner violence, income, occupation, history of the previous mental disorder, antenatal follow-up, complications during pregnancy, age of mother during pregnancy, conflict, and social support were found to be significantly associated with antenatal depression (Agostini et al., 2015; Beyene et al., 2021; Fekadu Dadi et al., 2020; Getinet et al., 2018).

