**Behavioral**

Smoking, chat chew, smoking

\\

,

Knowledge on IPV

IPVp

Attitude,

Controlling towards IPV

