**Couple Based Violence Prevention**

**Education**

**Community**

Social support

Inequitable gender norms

Autonomy (household decision making)

Self-efficacy

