**Questionnaire for husbands at baseline and end-line:** similarly, these questionnaires will be administered to husbands of pregnant women in two study groups. The questionnaire consists of information in terms of male partners individual characteristics, including age, levels of education, religion, occupation, marriage type, current alcohol use, current smoking status, women’s autonomy, self-efficacy, and household characteristics. Relational characteristics include the duration of marriage and disparity in educational attainment; community characteristics include the presence of social support. The societal characteristics of male partners include also decision-making power outcome measures such as partner’s knowledge, attitude, and control towards IPV.

**Focus Group Discussion (FGD) guides:** The guide will be used during FGD to collect qualitative information on male partners perspectives towards intimate partner violence, awareness and consequences of IPVs, risk and protective factors of IPV in pregnancy, and myths and misconceptions about intimate partner violence. Themes will be followed by several probes and questions to get a deep insight into the perpetration of IPV. The group discussion may take 60–90 minutes. Besides, the interview guides, tape recorder, and note book will be used during FGDs.

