| 217 | Does any member of this household own any agricultural land? | | | | | 1. Yes | | 2. No | | | | | | | | If yes, how many hectare? | | | | |  | |
| 218 | Does any member of this household own Radio? | | | | | 1. Yes | | 2. No | | | | | | | | If yes, how many? | | | | |  | |
| 219 | Does any member of this household own Television? | | | | | 1. Yes | | 2. No | | | | | | | | If yes, how many? | | | | |  | |
| 220 | Does any member of this household own Telephone (Mobile)? | | | | | 1. Yes | | 2. No | | | | | | | | If yes, how many? | | | | |  | |
| 221 | Does any member of this household own table? | | | | | 1. Yes | | 2. No | | | | | | | | If yes, how many? | | | | |  | |
| 222 | Does any member of this household own chair? | | | | | 1. Yes | | 2. No | | | | | | | | If yes, how many? | | | | |  | |
| 223 | Does any member of this household own bed with cotton/sponge/spring mattress? | | | | | 1. Yes | | 2. No | | | | | | | | If yes, how many? | | | | |  | |
| 224 | Does any member of this household own a solar lamp? | | | | | 1. Yes | | 2. No | | | | | | | | If yes, how many? | | | | |  | |
| 225 | Does any member of this household own watch? | | | | | 1. Yes | | | | 2. No | | | | | | If yes, how many? | | | | |  | |
| 226 | Does any member of this household own bicycle? | | | | | 1. Yes | | | | 2. No | | | | | | If yes, how many? | | | | |  | |
| 227 | Does any member of this household own motor? | | | | | 1. Yes | | | | 2. No | | | | | | If yes, how many? | | | | |  | |
| 228 | Does any member of this household own animal-drawn cart? | | | | | 1. Yes | | | | 2. No | | | | | | If yes, how many? | | | | |  | |
| 229 | Does any member of this household have a bank account? | | | | | 1. Yes | | | | 2. No | | | | | | If yes, how many? | | | | |  | |
| 230 | Does any member of this household own khat farm? | | | | | 1.Yes | | | | 2.No | | | | | | If yes, how many hectare? | | | | |  | |
| 231 | Does any member of this household own eucalyptus farm? | | | | | 1.Yes | | | | 2. No | | | | | | If yes, how many hectare? | | | | |  | |
| 232 | How many quintals of the following cereals do the family produced in this year? | | | | | 1.Teff-- | | | | 3.Maize--------- | | | | | | 5. Barley  ---------- | | | | |  | |
|  |  |  |  |  |  | 2.Millet ----- | | | | 4. Wheat ……. | | | | | | 6. others, Specify | | | | |  | |

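### Inequitable gender norms is a listed independent variable that no form measures, and khat chewing is in the conceptual framework but no form asks about it

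*Protocol*

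**What the plan says.** The first specific objective in section 5.3.2 is "To assess the prevalence and associated factors of IPV during pregnancy". Section 6.6.2 sets out the independent variables by ecological level and gives the community level as "presence of social support and inequitable gender norms". The conceptual framework (Figure 2) also shows "Inequitable gender norms" as an entry of its own, beside social support, autonomy and self-efficacy.

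Section 6.17 defines how violence, social support, knowledge, attitude, controlling behaviour, autonomy and self-efficacy are measured. Section 6.21 describes the content of the forms; for husbands it says that "community characteristics include the presence of social support" and names nothing else at that level.

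On khat, the behavioural part of the framework reads "Smoking, chat chew, smoking". The literature review reports, from one Ethiopian study, that "partner who chews chat and partner smoking status" were among the factors significantly associated with violence during pregnancy. The khat question in the women's form, item 230, is "Does any member of this household own khat farm".

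**The concern.** A variable named as an explanatory factor needs a question, or a rule for deriving it from other questions. For gender norms the protocol gives neither. A covariate list can be settled later in an analysis plan, but data that no form collects cannot be recovered there. If the forms are fielded as annexed, Objective 1 will be reported without a factor that the protocol says it will study. Table 2 and the session schedule in Appendix IV also give session 3 to this construct, so the trial would teach couples to challenge these norms without recording them.

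Khat chewing is the lesser part. The protocol's own review cites it as associated with the outcome, and the women's form already asks about the husband's smoking and drinking, so leaving it out looks like an oversight rather than a decision.

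**Working it through.** The protocol states no figure on this point, so there is none to reproduce. The check matches each variable in 6.6.2 to an item in the English women's form (Annex II), then looks for the unmatched ones in the husbands' form (Annex III), the Amharic forms (Annexes VI and VII), section 6.17 and section 6.21.

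| Level | Listed in 6.6.2 | Source items in Annex II | Unmatched |
|---|---|---|---|
| Individual | 12: wife's age, age at marriage, age difference, education, occupation, parity, alcohol, sex of previous children, birth order, smoking, previous antenatal care, place of delivery | 101, 102, 105, 110–113, 115, 116, 301, 302, 306, 407 | 0 |
| Relational | 3: marriage type, duration of marriage, education disparity | 117, 104, 110 with 111 | 0 |
| Community | 2: social support, inequitable gender norms | 507–509 for social support | 1 |
| Societal | 1: household wealth index | 201–235 | 0 |

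Listed: 12 + 3 + 2 + 1 = 18. Matched or derivable: 12 + 3 + 1 + 1 = 17. Unmatched: 18 − 17 = 1, inequitable gender norms.

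Some matches are thin. Item 301 serves both parity and birth order, item 407 covers only the child before this pregnancy, and items 115 and 116 cover the husband only. They are matches all the same.

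**Gender norms elsewhere.** Section 6.17 has no entry for them, and section 6.21 does not mention them for wives or husbands. None of the four forms has a norms item. Three item sets come near, and section 6.17 assigns each to another variable:
- the questions on when a husband is justified in hitting his wife (612–616) are Attitude;
- the controlling items (618–623) are Controlling behaviour;
- the decision-making items (501–505) are Autonomy.

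The framework shows norms, attitude and autonomy as separate entries, so none of these sets is the designated measure of norms.

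**Khat.** Three places set side by side:
- Framework: chewing is listed under behavioural factors, with no person named.
- Literature review: partner chewing is reported as associated with violence in pregnancy.
- Forms: the husband's smoking (115) and alcohol use (116) are asked. Khat appears only as farm ownership (230), within the household assets. No form asks whether either partner chews.

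Khat chewing is not among the 18 variables of 6.6.2, so this gap lies between the framework and the forms. It does not add to the count above.

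**The case against.** The strongest reply is that this is one unmatched variable in 18, in a secondary, descriptive objective. Section 6.24 states no associated-factors regression or covariate set for Objective 1, and the choice of covariates commonly belongs in an analysis plan. A protocol need not measure every factor its review cites: partner aggressive behaviour and childhood abuse are also cited and have no item. Khat is not in 6.6.2 at all, and the framework entry is text recovered from a figure whose layout is lost.

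Much of this stands, and it sets the limits of the point. It does not remove it, because gender norms is in the protocol's own variable list and the missing data cannot be created at analysis. The reply is stronger on khat, which rests on the framework and the review only.

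Four stronger readings are tempting, and the documents do not support them:
- *That the ecological model cannot be fitted.* Seventeen of 18 variables are available and all four levels keep at least one. Only the model exactly as listed is out of reach.
- *That half the community level is missing.* This holds for 6.6.2 (one of two). In the framework the community part has four entries and three are measured, so the shortfall there is one in four.
- *That using the attitude items would adjust for an outcome.* Attitude is a secondary outcome of the trial comparison, but Objective 1 has violence as its dependent variable. Section 6.21 has the forms administered before any education session, so baseline attitude is a legitimate explanatory factor. The protocol also never proposes it as a stand-in for norms.
- *That partner khat chewing is in the framework.* The framework does not say whose chewing is meant; the partner is named only in the review. The Annex V handout lists chewing among the consequences for the woman, so the person cannot be assumed.

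**Conclusion.** The point holds in a limited form. One of the 18 independent variables in 6.6.2, inequitable gender norms, has no definition, scale or question, so the associated-factors analysis cannot include it as listed. Khat chewing is in the framework, and the review supports partner chewing as a factor, but no form records it. The primary outcome, the sample size and the randomised comparison are not touched. How far the adjusted associations in Objective 1 would change cannot be computed from the documents. This is a low-priority correction, worth making because it is cheap before baseline and cannot be made afterwards.

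The conclusion assumes that the annexed English and Amharic forms are the ones to be fielded and that the planned Hadiyisa translation adds no items. The last pages of the protocol were not available for the check.

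**What to change.** Before baseline:
1. Add a short, fixed set of gender-norm statements to the women's and husbands' forms, and put the scoring rule in section 6.17. Failing that, remove inequitable gender norms from 6.6.2, so that Objective 1 does not claim to assess it. The framework can keep the construct, since the education sessions address it.
2. Add one yes/no item on the husband's current khat chewing beside the smoking and alcohol items of the women's form (115–116 in English, 114–115 in Amharic).
3. Carry the new items through the translation and pre-test that are already planned.

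The attitude items need no restriction for Objective 1. The cost is a few questions and a slightly longer interview, or one deletion. If baseline has already been collected on the annexed forms, only the deletion remains, and the Objective 1 report should say that gender norms and khat chewing were not measured.
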